## Abstract

**Background:**

The use of peripherally inserted central catheters (PICC) has increased due to its benefits, such as greater durability, safety, comfort, and cost-effectiveness. Technological advancements, such as catheter tip navigation systems and the use of ultrasound, have improved its quality. However, complications still occur, including infections and thrombosis, especially in oncology and intensive care patients. Studies indicate that advanced practices, technology, and specialized teams reduce these risks. New techniques, such as tunneled insertion, show potential for reducing complications, but further research with larger samples is needed to validate these findings.

**Objective:**

To compare the tunneling technique of PICC to non-tunneling insertion technique regarding the incidence of isolated or combined outcomes of catheter-related bloodstream infection, thrombosis, occlusion, and accidental dislodgement in the adult population within a 30-days period.

**Materials and methods:**

In this randomized, parallel, multicenter clinical trial, 840 patients from three reference hospitals will be assigned to two parallel groups (conventional PICC and tunneled PICC groups) through computer-generated stratified randomization. The conventional group will undergo PICC insertion according to routine practice. In the tunneled PICC group, an additional subcutaneous tunneling procedure will be performed. Patients will be followed until PICC removal for any reason or 30 days after insertion, whichever occurs first. The primary outcome is to assess whether subcutaneous tunneling reduces the rate of isolated or combined adverse events (infection, thrombosis, obstruction, and dislodgement) compared to the conventional method.

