## Introduction

The use of peripherally inserted central catheters (PICCs) has grown in recent years due to their advantages over other catheters. Research highlights benefits such as longer dwell times, durability, safety, comfort, versatility [1,2], and cost-effectiveness [3]. Industry advancements in materials (polyurethane, polyethylene) and technology have further driven adoption. Innovations include tip navigation and location systems [4], ultrasound, micro-introduction, and the Modified Seldinger Technique [5,6].

However, despite all these technical advancements and the deepening of knowledge related to the use of PICC, this device is not free from risks. Major complications, such as thrombosis and infection, and minor complications, such as phlebitis, accidental traction, and catheter displacement, can occur at varying rates depending on the study population. In adults, studies indicate catheter-related infection rates ranging from 0.07 to 2.46 per 1000 catheter-days, which are more common in oncology and intensive care patients [7,8].

Regarding thrombosis, patients with hematologic cancer are more predisposed to this condition, with incidence rates varying from 2% to 75% [9–12]. However, it is noteworthy that these rates can be reduced with the use of higher-quality devices, advanced technology, vascular access specialist nurses, and the adoption of best practices in both insertion and maintenance [13]. A multicenter study conducted in 16 centers in Brazil on patients with PICCs supports these findings, showing low complication rates, such as catheter-related bloodstream infection, venous thrombosis, and reversible occlusion [14].

While technology, vascular access teams, best practices, and infection control bundles have reduced PICC-related complications, new insertion techniques can further minimize risks. Studies support the tunneling technique over conventional insertion [15,16]. A randomized clinical trial (RCT) found tunneled PICCs had longer dwell times and lower thrombosis and infection rates [16], with another RCT confirming reduced thrombosis and accidental tractions [17].

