### Outcomes

**Catheter-related primary bloodstream infection:** bloodstream infection in a patient using a peripherally inserted central catheter (PICC) for more than two days (with the first day being the day of catheter insertion) and diagnosed with infection either while the catheter is still in use or within one day after its removal [19].

**Catheter-related thrombosis:** formation of thrombi inside the vein leading to obstruction of blood flow. Diagnosis should be made using appropriate imaging exams (venous ultrasound and/or venous Doppler), associated or not with the following signs and symptoms: pain, swelling, redness, dilated superficial veins, impaired limb movement, low-grade fever [20].

**Irreversible catheter occlusion:** Catheter occlusion is characterized by the blockage of the lumen due to the formation of a blood clot or precipitate of medications, preventing the infusion of intravenous solution [20].

**Accidental catheter dislodgement: C**haracterized by the accidental partial or total exteriorization of the catheter by a healthcare team member or the patient themselves, rendering the catheter unusable. Inviability of the catheter is defined by the improper positioning of the distal end of the catheter outside the cavoatrial junction, where positioning of the catheter is mandatory [20].

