### Recruitment

When an adult patient needs a peripherally inserted central catheter (PICC), the medical or nursing team will notify researchers via electronic systems or medical prescriptions with patient details. The research team will assess eligibility, invite qualifying patients, and obtain informed consent. Participants will be randomly assigned to study groups. Recruitment started on May 6, 2024 and will be completed on December 31, 2025. The data collection will be finished in 30 days after the last inclusion.

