### Statistical methods

The data will be entered and analyzed using the Statistical Package for the Social Sciences (SPSS) version 24.0. Initially, a Shapiro-Wilk test will be conducted to assess the normality of continuous variable distributions. Following this stage, a descriptive analysis will be performed, in which results will be reported as mean ± standard deviation (SD), median (P25 - P75), or as absolute and relative frequencies, depending on the characteristics and distribution of the variables.

The quantitative variables between groups will be compared using either Student’s t-test or the Mann-Whitney U test, depending on the data distribution. Pearson’s Chi- square test will be employed to assess associations between the clinical characteristics of patients and devices with events during follow-up. Groups will be compared for device event-free survival using Cox proportional hazards analysis and the log-rank test.

Other associations will be analyzed based on data distribution and appropriate statistical tests. A two-tailed P < 0.05 will be considered statistically significant.

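### Follow-up ends at PICC removal, but the infection definition runs one day past removal and the thrombosis definition is not tied to a catheter in place, so some primary-outcome events fall outside the observation window

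*Protocol article*

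**What the plan says.** Four places in the protocol article bear on the observation window.

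- **Abstract, Materials and methods:** "Patients will be followed until PICC removal for any reason or 30 days after insertion, whichever occurs first". This is the only statement of the follow-up rule in the text at hand.
- **Abstract, Objective:** the two techniques are compared on the isolated or combined outcomes "in the adult population within a 30-days period".
- **Outcomes, infection:** the infection must be "diagnosed with infection either while the catheter is still in use or within one day after its removal".
- **Outcomes, thrombosis:** "Diagnosis should be made using appropriate imaging exams (venous ultrasound and/or venous Doppler", with or without symptoms. No time limit is given, and the catheter need not be in place.

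The other two components differ. Dislodgement is an event "rendering the catheter unusable", and occlusion is a blocked lumen that prevents infusion; both presuppose a catheter in place.

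The Recruitment section says "The data collection will be finished in 30 days after the last inclusion", which dates the end of data collection for the whole trial and does not extend any patient's follow-up. The Blinding section says that data may be collected from electronic medical records.

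**The concern.** Infection and thrombosis are two of the four components of the primary composite. For both, the definition admits events that occur after the stated end of follow-up.

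Two consequences follow. First, if a catheter is removed because a complication is suspected and the culture or scan is reported afterwards, the event that prompted removal may go uncounted. The document does not say how often this would happen. Second, two centres could act differently in good faith: one counts a next-day infection because the definition includes it, and another does not because follow-up has ended. An analysis plan can settle how to count recorded events, but it cannot recover events that were never collected.

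**Working it through.** **1. The passages side by side**

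| Component | Can it qualify after removal? | Observed under the stated rule? |
|---|---|---|
| Infection | Yes, to one day after removal | No, once the catheter is out |
| Thrombosis | Yes; no catheter-in-place condition, and the objective runs to 30 days | No, if imaged after removal |
| Occlusion | No | Not affected |
| Dislodgement | No | Not affected |

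The infection row is an explicit contradiction. The thrombosis row is a gap that arises because the definition sets no limit. The infection conflict also arises for a catheter removed on day 30 itself, since the definition then reaches day 31.

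**2. The one-day infection gap**

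Inputs: 0.07 to 2.46 infections per 1000 catheter-days (Introduction) and 840 patients (Sample size). Assumption: the in-use rate applies on the day after removal, and every patient has one such day.

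- Low: 0.07 × 840 / 1000 = 0.06 infections
- High: 2.46 × 840 / 1000 = 2.07, about 2.1 infections

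The rate could be higher on the day after a removal for suspected infection, but the document gives no figure for that.

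**3. The plan's own sample size**

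Inputs: relative risk 0.5, 80% power, two-sided 5%, 840 in total including 10% for losses. No control risk is stated, so 840 cannot be reproduced directly. Solving backwards with the usual two-proportion formula without continuity correction, a control risk of 11.3% gives 381 per group, 762 in total. That becomes 839 as 762 × 1.10, or 847 as 762 / 0.9. The figure of 840 is therefore reachable, and no error in it is shown.

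**4. Illustrative effect of missed events on power**

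Evaluable per arm: 420 × 0.9 = 378. Formula: power = Φ(|p₁ − p₂| / √{[p₁(1 − p₁) + p₂(1 − p₂)] / 378} − 1.96), with p₂ = p₁ / 2. A share of events is assumed to be missed equally in both arms.

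| Missed (assumed) | p₁ | p₂ | Difference / SE | Power |
|---|---|---|---|---|
| 0% | 0.1130 | 0.0565 | 0.0565 / 0.02015 = 2.80 | 80% |
| 5% | 0.1074 | 0.0537 | 0.0537 / 0.01969 = 2.73 | 78% |
| 10% | 0.1017 | 0.0509 | 0.0509 / 0.01922 = 2.65 | 75% |

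For scale, the full 840 would be expected to yield 420 × (0.113 + 0.0565) = 71 events. The upper infection figure of 2.1 is about 2.1 / 71 = 3% of these, if each were a patient's first event. Any larger loss would have to come from thrombosis or from a higher infection rate around removal.

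**The case against.** The case against making much of this has several good points.

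- **The explicit conflict is narrow.** It is one day for one component. Thrombosis is affected only because its definition is open-ended. This stands.
- **The stopping rule is one sentence in an abstract.** The participant timeline (S3 Table) is not shown, and record-based collection could in practice pick up a culture or scan ordered at removal. This stands as a caution: one can say what the rule leaves out if followed as written, not that events are in fact being lost. But no section at hand states a different rule.
- **Following patients until removal or day 30 is a coherent design for a device trial.** The 30 days could be read as a cap on time with the catheter in place. That is a fair reading of the objective, but the infection definition still conflicts with it, and the thrombosis definition would have to say so.

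A reader might go further and infer that unequal dwell time severely weakens the trial. The Introduction reports a cited trial in which "tunneled PICCs had longer dwell times and lower thrombosis and infection rates", and follow-up here lasts only as long as the catheter. Take assumed mean times to event-free removal of 12 days (control) and 15 days (tunneled), a daily hazard ratio of 0.5 and a control incidence of 11.3%. The tunneled incidence is then 6.96%, the crude risk ratio 0.62, and the power of a comparison of proportions about 54 to 55%. The document does not support drawing that conclusion, for three reasons.

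- The Statistical methods section plans a time-to-event comparison: "Groups will be compared for device event-free survival using Cox proportional hazards analysis and the log-rank test". With censoring at removal, the same scenario yields 378 × (0.113 + 0.0696) = 69 events, and log-rank power is Φ(√69 / 2 × ln 2 − 1.96) = Φ(0.92), about 82%. This takes removal as unrelated to event risk, as does the scenario behind the 54%.
- Following patients to day 30 does not equalise dwell time. Occlusion and dislodgement still need a catheter, and infection still ends one day after removal.
- The dwell result belongs to one cited trial. It is not a stated expectation of this one, whose hypothesis does not mention dwell time.

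**Conclusion.** The follow-up sentence, the infection and thrombosis definitions and the 30-day objective do not agree, and nothing else in the article reconciles them. Followed as written, the rule excludes infections diagnosed the day after removal and thromboses imaged between removal and day 30. Occlusion and dislodgement are not affected.

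The size of the loss is unknown. The infection gap alone is small at the cited rates. The number of missed thromboses cannot be derived from the document. The fall in power to about 78% or 75% is an illustration that rests on three assumptions: the back-solved control risk, 378 evaluable patients per arm, and an equal 5% or 10% loss in both arms. It is not an estimate. Should removal times or reasons differ between arms, the loss could also differ by arm; the document gives no basis for sizing that.

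The point is worth acting on because it concerns the definition of the primary outcome and is cheap to repair while records remain available.

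**What to change.** Reconcile the Objective, the follow-up sentence and the Outcomes section by amending the follow-up sentence, for example:

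*Outcome ascertainment continues after PICC removal through the medical records. Bloodstream infection is counted to one day after removal, as defined. Catheter-related thrombosis is counted to day 30 after insertion. Occlusion and dislodgement are counted while the catheter is in place, to day 30. The date and reason of removal are recorded for every participant.*

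State whether a removal on day 30 carries the infection window to day 31. Apply the amended rule by record review to participants already enrolled, with the reviewers blinded to allocation as the Blinding section intends.

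The cost is a short amendment and some extra record review. Records are already a data source, and data collection is already planned to run to 30 days after the last inclusion, so at most a day or so would be added for the last participants. The amendment should not be presented as a remedy for unequal dwell time, which it leaves unchanged.

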Based on this, we understand that there is a lack of studies with robust methodologies, especially those with larger sample sizes, to corroborate the current results. Similarly, few studies demonstrate the combined impact of tunneled PICC insertion on reducing negative outcomes. Therefore, we test the hypothesis that tunneled PICCs have lower rates of the combined or isolated outcomes like catheter-related bloodstream infections, thrombosis, occlusion, and accidental traction compared to PICC inserted using the conventional technique in the adult population of three large hospitals involved in the RCT.

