### Sample size

The sample size calculation considered a composite outcome including primary bloodstream infection related to the catheter, thrombosis, catheter obstruction, and accidental catheter traction. Sample size was calculated to detect differences in proportions between the control and intervention groups using the online tool PSS Health version [21], with a statistical power of 80%, a significance level of 5%, and a relative risk of 0.5 [22], indicating a 50% reduction in composite outcomes. The calculated sample size, with an additional 10% for potential losses, totals 840 subjects, divided equally (420 each) between the two groups across the three institutions.

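### The primary outcome is worded as isolated or combined events, so on a literal reading either the composite or any single component could be claimed as primary success, although only the composite was used to size the trial

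*Protocol article*

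**What the plan says.** Three places in the protocol article state what the trial sets out to show, and each joins the composite and its parts with 'or':

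- Abstract, Objective: the techniques are compared on the "incidence of isolated or combined outcomes of catheter-related bloodstream infection, thrombosis, occlusion, and accidental dislodgement" within 30 days.
- Abstract, Materials and methods: the primary outcome is whether tunneling "reduces the rate of isolated or combined adverse events (infection, thrombosis, obstruction, and dislodgement) compared to the conventional method".
- Introduction, last paragraph: the hypothesis is that "tunneled PICCs have lower rates of the combined or isolated outcomes like catheter-related bloodstream infections, thrombosis, occlusion, and accidental traction".

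The Outcomes section defines the four events one by one. It neither defines a composite nor names any outcome as primary.

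The Sample size section uses the composite only: "The sample size calculation considered a composite outcome including primary bloodstream infection related to the catheter, thrombosis, catheter obstruction, and accidental catheter traction". It is calculated "with a statistical power of 80%, a significance level of 5%, and a relative risk of 0.5", giving 840 patients with 10% added for losses.

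Statistical methods names Cox and log-rank analysis of event-free survival for comparing the groups, and closes with one general threshold: "A two-tailed P < 0.05 will be considered statistically significant". It does not say which comparison settles the primary question.

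**The concern.** A primary outcome has to tell the reader in advance which result counts as success. Here the wording leaves open whether there is one primary comparison (the composite) or five (the composite and four components). The sample size section points to one. The objective and the hypothesis, the latter speaking of rates and outcomes in the plural, permit five.

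At stake is what may be claimed at the end. If the composite shows nothing but one component, say dislodgement, reaches P = 0.04, the hypothesis as written can be called supported. In that case the 5% level used for the sample size would no longer be the false-positive rate of the trial's primary claim.

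**Working it through.** **1. The stated sample size and the missing control rate.** The inputs from Sample size are 80% power, 5% significance, relative risk 0.5, 10% for losses, and 840 in total (420 per arm). The control risk is not given, so 840 cannot be reproduced directly; it can only be solved backwards. The two-sided formula with pooled variance and no continuity correction is

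n per arm = [1.96·√(2p̄(1−p̄)) + 0.8416·√(p₁(1−p₁) + p₂(1−p₂))]² / (p₁−p₂)².

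With p₁ = 0.113, p₂ = 0.0565 and p̄ = 0.08475:

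- first term 1.96 × 0.3939 = 0.772
- second term 0.8416 × 0.3918 = 0.330
- n = (1.102)² / 0.0565² ≈ 380 per arm, or about 760 in all
- with losses: 760/0.9 ≈ 845, or 760 × 1.1 ≈ 837

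These bracket 840, so the plan is consistent with a control composite risk of about 11.3%. With a continuity correction it would be about 12.2-12.4%. Evaluable patients after 10% losses: 420 × 0.9 = 378 per arm.

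**2. Error rate if five comparisons may each carry the claim.** For five independent tests:

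- at least one two-sided P < 0.05: 1 − 0.95⁵ = 22.6%
- at least one false finding of benefit: 1 − 0.975⁵ = 11.9%

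The composite is correlated with its parts, so these overstate the figures. I therefore simulated trials with no effect: 378 per arm, four mutually exclusive components plus their sum as the composite, Pearson chi-square at two-sided 5%, 200,000 replicates per row. The component splits are assumptions; each sums to 11.3%.

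| Assumed component risks | Any of five, two-sided | Any of five, favouring tunneling | Composite alone, two-sided |
|---|---|---|---|
| 2.825% each | 20.3% | 10.5% | 5.0% |
| 1, 2, 3, 5.3% | 19.3% | 10.0% | 5.0% |
| 0.5, 2, 2, 6.8% | 18.6% | 9.6% | 4.9% |
| 7.1, 1.4, 1.4, 1.4% | 18.3% | 9.3% | 4.9% |

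In 13-15% of these null trials a component was significant, in either direction, while the composite was not. In 7-8% that happened in favour of tunneling, which is the result the literal wording would allow to be claimed.

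**3. Comparing the remedies.** With the composite as the single primary outcome, the error rate is 5% and the planned power is unchanged. Keeping all five as alternatives under Bonferroni (0.05/5 = 0.01 each) lowers composite power at a control risk of 11.3% to about 58%. Restoring 80% would take 1,134 evaluable patients, or 1,134/0.9 = 1,260 recruited.

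**The case against.** The best reply is that the phrase may simply describe a composite: a patient has any of the four events, alone or together. The Abstract speaks of a single rate, the sample size is built on the composite, and event-free survival in Statistical methods is most naturally time to first event. The section lists no five between-arm tests, and its chi-square test is described for patient and device characteristics against events. A multiplicity rule may also sit in an analysis plan that is not shown.

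Much of this stands. The composite was probably intended, and the absence of an adjustment method is no finding here. But the hypothesis refers to rates of combined or isolated outcomes in the plural, the objective is worded alike, and Outcomes names no primary outcome. The either/or is in the article's own text.

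Two stronger readings are not supported:

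- A reader might infer that the trial has a 20% chance of false success. The five-test family is a possible reading, not a stated plan. The 20% also counts findings of harm, whereas the claim is directional, so the relevant figure is about 10% against 2.5%.
- A reader might infer that the article promises 80% power for isolated events. It does not: Sample size already ties the 80% to the composite.

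**Conclusion.** The point holds as a badly fixed primary outcome: three statements allow the composite or any one component to carry the claim, while the trial is sized on the composite alone. If that latitude were used across all five comparisons, the chance of some two-sided P < 0.05 under no effect would be about 18-20% rather than 5%, and of a false claim of benefit about 10% rather than 2.5%, roughly a fourfold rise in each.

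The size rests on a back-solved control risk, assumed component splits, mutually exclusive events and a five-test family that the article does not list. It illustrates what the wording permits and is not an established error rate of this trial. The need to settle the wording does not depend on the exact figure.

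**What to change.** - Delete 'isolated or' (and 'or isolated' in the hypothesis) from the objective, the hypothesis and the primary outcome.
- In Outcomes, define the composite as occurrence of any of the four events within the 30-day follow-up, and name it as the single primary outcome, tested at two-sided 5%.
- Make the four components secondary, reported as event counts and effect estimates with 95% confidence intervals. No primary success claim attaches to them. If tests are wanted, use Holm across the four, and only after a significant composite.
- Bring the registry entry into line if it carries the same wording.

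The cost is a wording amendment, with no further patients or data. The price is that a lone significant component can no longer be claimed as primary success. The change should be made and dated before any unblinded analysis, because a primary outcome chosen afterwards would be open to the charge that the data chose it.
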